**Methods:**

A single-blind, randomized controlled trial comparing the ØCD prevention program to a waitlist control group will be conducted. Participants, at-risk adults (18–65 years) with subclinical OCD symptoms (OCI-R score ≥ 12), will be recruited for the study. The ØCD prevention program compresise of six online group sessions incorporating CBT and ERP techniques over three modules. The primary outcomes are OCD symptom severity (measured by the Obsessive-Compulsive Inventory- revised form; OCI-R), depression symptoms (measured by the Patient Health Questionnaire; PHQ-9), and anxiety symptoms (measured by the Generalised Anxiety Disorder 7-item; GAD-7). Secondary outcomes include OCD-related beliefs, experiential avoidance, resilience, quality of life, uncertainty intolerance, automatic thoughts, and distress. Outcome measures will be collected at baseline, at completion of the intervention, and one year later (follow-up). At follow-up, we will also analyze the OCD diagnostic incidence, using the Structured Clinical Interview for DSM-5. We will employ a multivariate analysis of variance (MANOVA) to explore whether significant differences exist between groups across dependent variables. To compare the OCD incidence levels from the pre-test to the follow-up we will use the chi-squared test.

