### Inclusion and exclusion criteria

Participants are included if they are of legal age (above 18). We include participants who have an OCI-R [10] score at or above the cut-off point on the OCD subscale (≥ 12). Exclusion criteria are as follows: (1) clinically diagnosed OCD, (2) current psychiatric/psychotherapeutic treatment, (3) a personality disorder diagnosis, and (4) suicidal ideation.

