### Outcome measures

For participants, the baseline assessment will take place after randomization and include a set of validated questionnaires.

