### Primary outcome measures

#### Obsessional Compulsive Inventory - Revised (OCI-R; [10])

OCI-R is a self-report questionnaire of 18 items, and it measures OCD symptoms across six subscales: washing, checking, neutralising, obsessing, ordering, and hoarding. OCI-R was used in the initial screening of eligible participants, where the OCD subscale (which excludes the hoarding component) was used to determine participants who are at risk of developing OCD symptoms (cut off point (≥ 12). For the present study, the reduction in OCI-R OCD subscale assessment is the primary outcomes.

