#### WHO Quality of Life - BREF (WHOQOL-BREF; [28])

WHOQOL-BREF is one of the most widely used assessments of quality of life. In the current study, we will use the global item of the instrument (How would you rate your quality of life), answered on a 5-point Likert scale.

Post-intervention assessment will take place immediately after the intervention is completed and will include the same measures, as well as the Client Satisfaction Questionnaire-8 (CSQ-8; [21]). The assessments will be completed online, using the Qualtrics platform. We will also perform one follow-up assessment six months later, using the same measures and the Structured Clinical Interview for DSM-5 to compare the OCD diagnostic incidence.

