### Statistical analyses

#### Data analysis

Demographic and clinical data will be reported as means and SDs for continuous parametric data, medians, and ranges for non-parametric data, and frequencies and percentages for categorical data. Only two authors will have access to the final trial dataset. To illustrate participant flow, we will report results in a CONSORT diagram. Data analysis will be conducted using SPSS for Windows version 25. Given the anticipated dropout rate, mixed models will be employed as the most suitable statistical method. This approach is well-suited for analyzing repeated measures, accounting for the dependency between observations and handling missing data effectively. Mixed models will be adjusted for baseline values of the repeated measures. Descriptive statistics will be generated to summarize the means and proportions of baseline clinical and demographic variables across treatment conditions, allowing for the assessment of potential imbalances. Fixed effects in the model will include time, treatment, and their interaction. In cases of missing data, these variables will also be included as fixed effects. The significance of the time*treatment interaction p-values for various outcome measures will be assessed using the Benjamini–Hochberg procedure (two-sided p < 0.05). Time will be treated categorically, with the first post-baseline measurement serving as the reference category. To address the correlation among repeated measurements, a first-order autoregressive (AR (1)) structure will be imposed on the residuals. Furthermore, the interaction effect between time and group will be explored by analyzing estimated marginal means at different time points. We anticipate a significant interaction effect between time and group, signifying differential changes in scores over time between the two treatment conditions. Specifically, we expect a more pronounced decline in scores over time in the prevention group compared to the control group. To assess the statistical significance of improvements in the treatment conditions, a least significant difference test will be conducted with estimated marginal means to compare changes between groups. Linear mixed models are expected to reveal a statistically significant decline in the prevention condition from pretest to post-test, with no significant differences between post-test and follow-up measures. To facilitate comparisons with other studies, Cohen’s d statistic will be calculated to determine within-group effect sizes. In cases where the proportion of missing data exceeds 10%, maximum likelihood imputations will be performed based on demographics and pretreatment scores. Additionally, the proportions of dropouts and diagnostic incidence (from pre-test to follow-up) in the two treatment groups will be compared using the chi-square test.

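### OCD diagnostic incidence is compared between arms by an unadjusted chi-square although a pre-randomisation OCI-R score exists for everyone: a modest loss of precision, not bias

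*Protocol article*

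**What the plan says.** The Data analysis section fixes the test: "the proportions of dropouts and diagnostic incidence (from pre-test to follow-up) in the two treatment groups will be compared using the chi-square test". The Abstract (Methods) agrees, without naming the arms: "To compare the OCD incidence levels from the pre-test to the follow-up we will use the chi-squared test". Neither place mentions a covariate. The diagnosis comes from a follow-up assessment "using the same measures and the Structured Clinical Interview for DSM-5 to compare the OCD diagnostic incidence".

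For the questionnaire outcomes the same Data analysis section takes a different course: "Mixed models will be adjusted for baseline values of the repeated measures".

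On the available covariate, the OCI-R paragraph under Primary outcome measures says that "OCI-R was used in the initial screening of eligible participants", and that its OCD subscale "was used to determine participants who are at risk of developing OCD symptoms". The Inclusion and exclusion criteria set the cut-off at 12 or more and state no upper limit. Procedure and randomization checks eligibility on the screening form and then allocates 1:1, with no mention of stratification by severity. The baseline battery comes later: under Outcome measures, "the baseline assessment will take place after randomization and include a set of validated questionnaires".

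**The concern.** All other efficacy outcomes are self-report scores. The interview diagnosis is the one outcome that shows directly whether fewer people developed OCD, which is the trial's stated purpose. It is also binary, probably with few events, and rests on about 88 to 100 people per arm, so information is scarce. A 2×2 chi-square cannot use differences in entry severity between participants. If the screening score predicts later diagnosis, an adjusted analysis of the same people has more power at no cost in data. The test is named in the article, so this is a stated choice and not a detail left to a document that is not shown.

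**Working it through.** **1. The plan's own figures.** The article gives no incidence, effect or power for this comparison. Its only sample-size figure is 175, for d = 0.3, α = 0.05 and power 0.95. For two arms and a two-sided test, 2 × (1.960 + 1.645)² / 0.3² ≈ 289 per arm, or 578 in total, so 175 does not follow from those inputs. That is a separate matter. Here 175 only supplies a plausible analysed number: 175 / 2 = 87.5, taken as 88 per arm. The target is 100 per arm.

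**2. Power of the planned chi-square.** With p̄ the mean of the two proportions p₁ and p₂, and n per arm:

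power ≈ Φ{ [ |p₁ − p₂| − 1.96 √(2 p̄(1 − p̄)/n) ] / √( [p₁(1 − p₁) + p₂(1 − p₂)]/n ) }

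For 10% versus 5% with n = 87.5: (0.05 − 1.96 × 0.0398) / 0.0396 = −0.71, so power is 0.24. A halved incidence, assumed throughout, gives:

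| Incidence | n = 87.5 | n = 100 |
|---|---|---|
| 5% vs 2.5% | 0.14 | 0.15 |
| 10% vs 5% | 0.24 | 0.27 |
| 20% vs 10% | 0.46 | 0.51 |
| 30% vs 15% | 0.66 | 0.72 |

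**3. Gain from adjustment, by odds ratio (OR) per SD of the score.** Simulation with 6,000 runs per scenario, 88 per arm, right-skewed score and two-sided 0.05. Pearson's chi-square is set against the logistic score test of arm adjusted for the score, so both tests belong to the same family. Entries are chi-square power → adjusted power.

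| Incidence | OR 1.0 | OR 1.5 | OR 2 | OR 3 |
|---|---|---|---|---|
| 5% vs 2.5% | 0.125 → 0.134 | 0.120 → 0.133 | 0.121 → 0.146 | 0.119 → 0.151 |
| 10% vs 5% | 0.231 → 0.237 | 0.236 → 0.246 | 0.239 → 0.259 | 0.228 → 0.284 |
| 20% vs 10% | 0.457 → 0.466 | 0.461 → 0.475 | 0.458 → 0.502 | 0.453 → 0.557 |
| 30% vs 15% | 0.666 → 0.664 | 0.677 → 0.689 | 0.675 → 0.715 | 0.678 → 0.771 |

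The gain is about 1 point at OR 1.5, 2 to 4 points at OR 2 and 3 to 10 points at OR 3. The OR 1.0 column differs by up to about 1 point with no prognostic information at all, so the 1-point gains are close to nothing. With 10% in both arms, the type I error over the four ORs was 0.044 to 0.050 for the chi-square and 0.044 to 0.052 for the adjusted test.

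**4. The same check by correlation.** Let liability = ρ × score + √(1 − ρ²) × noise, with ρ the correlation within the enrolled sample. Score test, 88 per arm, 4,000 runs, ρ = 0.5:

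| Incidence | Normal score | Skewed score |
|---|---|---|
| 15% vs 5% | 62% → 67% | 62% → 70% |
| 20% vs 8% | 64% → 70% | 65% → 74% |
| 30% vs 15% | 69% → 75% | 66% → 74% |

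Further runs of this kind put the gain at about 5 to 10 points for ρ = 0.5 in these scenarios, and at about 1 to 3 points for ρ = 0.3. The two scales are linked by OR ≈ exp(1.7ρ/√(1 − ρ²)). This gives exp(0.98) ≈ 2.7 at ρ = 0.5 and exp(0.53) ≈ 1.7 at ρ = 0.3.

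**5. Effect of the entry cut-off.** Truncating a normal score to variance s² turns a population correlation ρ into ρs/√(ρ²s² + 1 − ρ²). If 12 were the population median (assumed), s² = 0.363 and 0.5 becomes 0.301/0.917 = 0.33. If it were the 70th percentile (assumed), s² = 0.264 and 0.5 becomes 0.28. A population correlation of 0.5 thus lands near 0.3 in the trial.

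**The case against.** The strongest reply is that nothing here is wrong. After 1:1 randomisation a chi-square on two proportions is a valid test, and baseline adjustment of repeated scores does not oblige the authors to adjust a single binary outcome. Incidence is listed neither as a primary nor as a secondary outcome, the hypotheses name only questionnaires, and the trial was not sized on it. The gain is small unless OCI-R predicts diagnosis well, and no source in the article says that it does. All of this stands. It limits the size of the point but does not remove it, because the change is almost free and concerns the only count of new diagnoses.

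A reader might infer more than the documents support:

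- **Bias.** Chance imbalance in entry severity is already covered by the test's type I error, which the simulations put near 5%. The missing adjustment costs precision only.
- **OCI-R as the best predictor collected.** The plan uses it as a risk marker but does not rank it against OBQ-44, IUS or the other scales.
- **Gains of 5 to 10 points as the expected result.** These need a correlation of 0.5 after truncation at 12, and control incidence of 15% or more.
- **Larger gains from a likelihood-ratio test.** Comparing it with Pearson's chi-square mixes two statistics. At zero correlation it still appeared to gain about 6 points at 5% versus 2.5% and about 2 points at 10% versus 5%.
- **Rescue of the comparison.** With low incidence it stays badly underpowered either way.

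**Conclusion.** The point holds as a cheap improvement. The plan fixes an unadjusted test where a prognostic, pre-randomisation covariate is very likely available for all participants. With 88 per arm the power gain is about 1 to 3 points at a within-sample correlation of 0.3, and about 5 to 10 points at 0.5 with control incidence of 15% to 30%. At 10% versus 5% or lower it is about 1 to 6 points, with power below 30% throughout. If the score does not predict diagnosis the gain is nil, and so is the harm. Truncation at 12 favours the lower figures.

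Incidence, effect and correlation are all assumptions. Incidence also depends on follow-up length, which the Abstract gives as one year and the outcome section as six months; these must be reconciled. The simulations tested a logistic score test. The penalised fit and the standardised risk difference proposed below were not simulated.

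**What to change.** In the Data analysis section, and in the Abstract to match, make the main incidence analysis a logistic regression of SCID-5 OCD at follow-up on arm and the continuous screening OCI-R OCD-subscale score. Name the screening score explicitly, because the baseline battery is completed after randomisation. Report the standardised (marginal) risk difference with a 95% CI, so that the quantity estimated remains the difference in incidence between arms. Provide for a penalised (Firth) fit if events are sparse. Keep the chi-square as a supporting analysis and for the dropout comparison.

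The cost is a sentence or two of text and a few lines of code, with no new data, visits or participants. Reporting becomes slightly more complex than a 2×2 table, and few events would call for the penalised fit. The change should be recorded on the registry, as the article foresees for modifications, before outcome data are examined by arm; a covariate added after an imbalance has been seen would look post hoc.

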### Procedure and randomization

Inclusion and exclusion criteria are verified based on the screening form completed by the participants. Eligible participants are randomly allocated to one of the two conditions in a 1:1 ratio. Randomization is conducted by a member of the research team, using the online tool, randomizer.org. The allocation sequence is generated through a computer-generated random sequence for the two study conditions. The following study personnel will remain blind to group allocation until the final data analyses are completed: principal investigator, data managers, and outcome assessors.

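### The planned OCD incidence from pre-test to follow-up is prevalence at follow-up, because no diagnostic interview at entry is described; a difference between arms cannot be read as prevented onset.

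*Protocol article*

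**What the plan says.** All references are to the protocol article.

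- **Endpoint and test.** Data analysis: "the proportions of dropouts and diagnostic incidence (from pre-test to follow-up) in the two treatment groups will be compared using the chi-square test". The abstract's Methods paragraph also plans a chi-squared comparison of OCD incidence running from pre-test to follow-up.
- **When the diagnosis is made.** Abstract: "At follow-up, we will also analyze the OCD diagnostic incidence, using the Structured Clinical Interview for DSM-5". The assessment schedule, at the end of the WHOQOL-BREF paragraph, describes the follow-up as "using the same measures and the Structured Clinical Interview for DSM-5 to compare the OCD diagnostic incidence". The interview is added there to the measures already in use.
- **Baseline.** Outcome measures: "the baseline assessment will take place after randomization and include a set of validated questionnaires".
- **Entry criteria.** Inclusion and exclusion criteria: "Exclusion criteria are as follows: (1) clinically diagnosed OCD". The OCI-R OCD subscale must be at least 12, and no upper limit is stated.
- **How they are checked.** Procedure and randomization: "Inclusion and exclusion criteria are verified based on the screening form completed by the participants".

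**The concern.** Incidence counts new cases among people shown to be free of the disorder at the start. The article describes nothing that shows this. The exclusion covers people who already carry a diagnosis, not people who meet criteria but were never assessed. Excluding people in current treatment does not remove untreated cases either. Participants are selected for a raised OCD symptom score with only a lower bound, so undiagnosed cases are plausible. The abstract calls the symptoms subclinical, but no stated criterion enforces that.

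This is the trial's only diagnostic outcome, and the program is presented as prevention for people at risk of developing OCD. If the follow-up proportion is reported as incidence, the error can go either way. Entry cases that persist in both arms dilute a real preventive effect. Entry cases that remit under the program produce a difference that is treatment of existing OCD but would be reported as prevention.

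**Working it through.** **Is there a pre-test diagnostic status to count from?** The interview is named in two places, both at follow-up. Baseline is questionnaires. The entry check is a participant-completed form applied to a criterion about existing diagnosis. Figure 2 is not shown, but its abbreviation list names no diagnostic interview. The text therefore gives no interview-based status at pre-test.

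**Inputs for size.** The plan has no figure for incidence or for undiagnosed OCD at entry, so there is nothing of its own to reproduce. From the Sample size section: 175 participants suggested (175/2, about 87 per arm) and a target of 100 per arm. From the Background: adult OCD prevalence of 0.7–3% in the general population. Everything else is assumed: new-case incidence, the share q of undiagnosed cases at entry (equal in both arms), and whether those cases persist.

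**Formulas.**
- Observed proportion = q × (share of entry cases persisting) + (1 − q) × true incidence.
- Power = Φ[(d − 1.96·se0)/se1], where d is the difference in observed proportions, se0 = √(2p̄(1 − p̄)/n), and se1 = √([p_c(1 − p_c) + p_t(1 − p_t)]/n). This is the probability of a two-sided 5% result in the program's favour.

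**Direction 1: dilution.** True incidence is 10% (control) versus 5% (program), and all entry cases persist. The observed proportions are q + (1 − q)·0.10 and q + (1 − q)·0.05, with 87 per arm for power.

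| q | Control | Program | Risk ratio | Entry cases as share of control "incident" cases | Power |
|---|---|---|---|---|---|
| 0 | 10.0% | 5.0% | 0.50 | 0% | 24% |
| 1% | 10.9% | 5.95% | 0.55 | 9% | 22% |
| 3% | 12.7% | 7.85% | 0.62 | 24% | 18% |
| 5% | 14.5% | 9.75% | 0.67 | 34% | 16% |
| 10% | 19.0% | 14.5% | 0.76 | 53% | 12% |
| 20% | 28.0% | 24.0% | 0.86 | 71% | 9% |

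Worked row, q = 10%: control 0.10 + 0.90 × 0.10 = 0.19; program 0.10 + 0.90 × 0.05 = 0.145; ratio 0.145/0.19 = 0.76; share 0.10/0.19 = 53%. With p̄ = 0.1675, se0 = 0.0566 and se1 = 0.0565, so power = Φ[(0.045 − 0.1110)/0.0565] = Φ(−1.17) = 12%.

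The rows at 1% and 3% lie within the article's own general-population range. The higher rows allow for a sample selected on symptoms.

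**Direction 2: treatment counted as prevention.** True incidence is 5% in both arms, so there is no effect on onset. Entry cases persist in the control arm and half remit under the program. Here n = 100 per arm.

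| q | Control | Program | Risk ratio | Chance of a significant result |
|---|---|---|---|---|
| 3% | 7.85% | 6.35% | 0.81 | 6% |
| 10% | 14.5% | 9.5% | 0.66 | 19% |
| 20% | 24.0% | 14.0% | 0.58 | 44% |

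Worked row, q = 20%: control 0.20 + 0.80 × 0.05 = 0.24; program 0.20 × 0.5 + 0.80 × 0.05 = 0.14. With p̄ = 0.19, se0 = 0.0555 and se1 = 0.0550, so Φ[(0.10 − 0.1087)/0.0550] = Φ(−0.16) = 44%.

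**The case against.** **The comparison is randomized.** Undiagnosed entry cases should be balanced on average, so apart from dropout the chi-square test validly compares the arms on OCD at follow-up. This stands. It limits the point to what the quantity is called and what may be inferred from it.

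**The primary outcomes are OCI-R, PHQ-9 and GAD-7.** Diagnostic incidence is not listed among the primary or secondary measures and carries no hypothesis in the Aim section. This also stands: those analyses are untouched.

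**The article is condensed.** The wording about pre-test could reflect an entry check set out in the full protocol, and the content of the screening form is not described. This carries some weight. But the article does state the exclusion, how it is verified, what baseline contains and when the interview is given, and together these contradict the endpoint's label.

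**The size rests on assumed rates.** This is true. Near the article's general-population range the distortion is modest, and power on this endpoint is low (24%) even with no entry cases. The loss of power is therefore a lesser concern than the interpretation.

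**Stronger readings.** A reader might infer that incidence could never be measured in this trial, that the test is invalid, or that many participants already have OCD. The documents support none of these. Onset could be dated, though imperfectly, in the interview already planned; randomization protects the comparison; and no figure for undiagnosed cases at entry is given.

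**Conclusion.** The point holds as one of labelling and interpretation. As written, the plan would report SCID-5 prevalence at follow-up as incidence since pre-test, and a difference between arms could be prevented onset, remission of existing OCD, or both.

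Under the assumed rates, a true risk ratio of 0.50 appears as 0.55 to 0.86 when 1% to 20% of participants are persisting entry cases. With no effect on onset at all, a ratio of 0.58 can arise if 20% are entry cases and half remit under the program. These figures show direction and plausible scale; they are not estimates for this trial. The conclusion that the label is wrong needs none of them. It follows from the stated timing of the interview and the stated entry check.

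**What to change.** **Main change.** In the abstract, in the assessment schedule and in Data analysis, rename the endpoint as the proportion meeting SCID-5 OCD criteria at follow-up. Report the arm difference with a 95% confidence interval, and do not describe this result as incidence or as prevention of onset. The name should carry one time point; the abstract gives one year and the assessment schedule six months, and these passages must be reconciled.

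**Sensitivity analysis only.** Have the blinded interviewer record the date of onset in the follow-up SCID-5 already planned. Count onset after randomization as incident, and remove cases of earlier onset from both numerator and denominator. To do this evenly, the question has to cover past as well as current OCD, so that entry cases that have since remitted are removed too.

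**Why this order.** Participants know their allocation, and the program teaches them what OCD is and has them monitor OCD-related thoughts. Recalled onset may therefore be misclassified differently by arm, and exclusions based on it could bias the contrast. A baseline interview for everyone is no longer available, since 121 participants had been randomized at submission.

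**Cost.** Wording changes in three places and a dated onset question in an interview already planned. The real price is a weaker headline: the diagnostic result would support a claim about OCD status at follow-up, not about prevented cases.

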## Article summary

Strengths and limitations of this study

• First study to develop and validate an OCD prevention program for at-risk adults.

• The program integrates psychological prevention techniques from evidence-based treatments.

• Moderate expected rates of participants dropout

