### Sample size

G*Power was used for the sample size calculation and, following an effect size of d=0.3 with a n alpha level of α = 0.05 and power of 0.95, a sample size of 175 was suggested. Based on this power analysis and expected drop-out rates, we aim for 200 participants (100 per treatment arm). The Consolidated Standards of Reporting Trials flow chart of the trial is shown in Figure 1.

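### OCD incidence is compared by an unadjusted chi-square on a single follow-up diagnosis, and no stated method uses the post-test scores when that diagnosis is missing

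*Protocol article*

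**What the plan says.** The Data analysis section states that "diagnostic incidence (from pre-test to follow-up) in the two treatment groups will be compared using the chi-square test". The abstract agrees: "To compare the OCD incidence levels from the pre-test to the follow-up we will use the chi-squared test". Neither place names a covariate or an analysis set for this test.

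After randomisation the diagnosis is sought once. The end of the Outcome measures section describes a single follow-up, "using the same measures and the Structured Clinical Interview for DSM-5 to compare the OCD diagnostic incidence". Before that, "Post-intervention assessment will take place immediately after the intervention is completed and will include the same measures", so OCI-R, PHQ-9 and GAD-7 are all collected between baseline and the diagnostic interview.

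Loss is anticipated. The Article summary lists "Moderate expected rates of participants dropout", and the Sample size section says "Based on this power analysis and expected drop-out rates, we aim for 200 participants (100 per treatment arm", against a calculated 175. No dropout rate is given.

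The Data analysis section handles dropout in two ways. Mixed models are chosen for the repeated measures because dropout is expected. Separately, when more than 10% of data are missing, values are imputed by maximum likelihood from demographic variables and scores taken before treatment. The text does not say whether this second rule extends to the diagnosis.

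The time of the follow-up is also inconsistent. The Outcome measures section has "We will also perform one follow-up assessment six months later", while the abstract has assessments "at completion of the intervention, and one year later (follow-up". The two must be reconciled, because the interval governs both how many people are lost and how many become cases.

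**The concern.** Incidence appears in neither the primary nor the secondary outcome list. It is nevertheless the trial's only direct measure of prevention, which is the stated aim, and the abstract announces it.

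The plan recognises dropout as a problem for the questionnaire scores and picks a method accordingly. For the diagnosis it names a two-by-two test, which can use only people with a diagnosis, observed or imputed. Suppose a participant's OCI-R has risen by the post-test and the participant then misses the interview. Without imputation that person leaves the comparison. With the stated imputation, the diagnosis is filled in as if the post-test score had never been seen.

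The arms may lose people for different reasons: one attends six sessions and the other waits. If loss depends on post-test symptoms differently by arm, the difference in incidence is distorted in either direction, even though the trial holds scores that could help correct it.

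**Working it through.** **1. Implied loss.** 1 − 175/200 = 25/200 = 12.5%, or about 12 to 13 people per arm of 100. This reproduces the article's allowance. Whether 175 follows from its own stated inputs is a separate matter and is not used here. A 12.5% loss would exceed the 10% trigger, if the trigger applies to the diagnosis at all.

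**2. The two readings of the imputation rule.**
- Rule does not cover the SCID: the chi-square is in effect complete-case.
- Rule covers the SCID: above 10% missing, the diagnosis is imputed from information that predates the programme. At 10% or less, the test is again complete-case.

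Under neither reading do the post-test scores inform a missing diagnosis.

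**3. Possible size of the bias without imputation.** The article gives no incidence, no link between score and diagnosis, and no dropout pattern. All of the following are assumptions:
- Post-test score S (SD units): mean 0 in the waitlist arm, −0.3 in the programme arm, SD 1.
- Caseness: logit P(case) = a + 1.2·S, with a = −2.708 so that waitlist incidence is 10.0%. Programme incidence is then 7.5%, a true difference of 2.5 points.
- Loss: logit P(missing) = c + b·S, with c set to give the chosen loss in each arm; b = 1 where loss depends on the score and b = 0 where it does not.
- Observed incidence = E[P(case)·(1 − P(missing))] / E[1 − P(missing)].

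Results at 12.5% loss per arm:

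| Loss depends on score in | Waitlist | Programme | Difference (points) |
|---|---|---|---|
| neither arm | 10.0% | 7.5% | 2.5 |
| waitlist only | 8.7% | 7.5% | 1.2 |
| programme only | 10.0% | 6.4% | 3.6 |
| both arms alike | 8.7% | 6.4% | 2.3 |

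At 10% loss, where the rule does not trigger, the last three differences are 1.4, 3.4 and 2.3 points. At 20% loss they are 0.6, about 4 and 2.1.

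**4. A second set of assumptions, with no true effect.** Incidence is 15% in both arms, the odds ratio for caseness is 3 per SD of post-test score, and the loss slope is 0.7. With opposite slopes in the two arms, a false difference of 2.0 points appears at 12.5% loss and 3.9 points at 25% loss. With the same slope in both arms the false difference is 0.

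**5. Scale against sampling error.** With 87.5 interviewed per arm, the standard error of the difference in step 3 is √(0.10·0.90/87.5 + 0.075·0.925/87.5) = 0.043, or 4.3 points. The shifts at 12.5% loss (2.5 − 1.2 = 1.3 and 3.6 − 2.5 = 1.1 points) are about 0.3 of a standard error. They are large relative to the assumed effect but modest relative to the trial's precision on this outcome.

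**The case against.** **The article never says the test is run only on those who attend the interview.** A reader might infer this, but the documents do not establish it. The imputation sentence immediately before the quoted one speaks of missing data in general, and at the implied 12.5% loss its trigger would be met. This stands against any claim that the plan fixes a complete-case analysis. It does not remove the point, because the predictors the rule names leave out the post-test scores.

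**A condensed article may leave the analysis set and imputation details to a fuller document.** That is fair for what is merely absent. Here the article itself states both the test and the imputation predictors, and the point concerns those stated choices.

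**Material bias needs loss that depends on scores differently by arm, and nothing in the documents shows that it will.** This stands. With the same pattern in both arms the difference barely moves (2.3 against 2.5 points). That post-test scores predict caseness is also an assumption, though a reasonable one, since the OCI-R measures OCD symptoms. The planned comparison of dropout proportions between arms would not reveal different selection at equal loss rates.

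**A reader might also infer that a few missing interviews would decide the result.** For example, 10/87 v 3/88 gives p = 0.041, and 10/100 v 4/100, with one more programme case among those lost, gives p = 0.096 (uncorrected chi-square). But 10/87 v 4/88, with nobody added, already gives p = 0.090. The sensitivity comes from rare events, and the example is no evidence of missing-data bias.

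**Incidence is not a listed outcome.** True, and it limits how much rests on this test. It does not make the result unimportant in a prevention trial.

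**Conclusion.** The point holds in a limited form. Incidence is compared without adjustment on a diagnosis made only at follow-up, the handling of a missing diagnosis is unclear, and neither reading of the imputation rule uses the post-test scores. On the assumed inputs, a true 2.5-point difference could appear as anything from 1.2 to 3.6 points at the implied 12.5% loss. That range requires score-dependent loss confined to one arm. The article supplies none of the incidence, slope or loss-pattern inputs, so these figures show what could happen and do not predict it. The conclusion that bias is present, or that the plan discards everyone who misses the interview, goes further than the text allows. The change is worth making because it is cheap and uses data the trial already collects.

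**What to change.** Reword the incidence analysis as follows:
- Analyse incidence in all randomised participants, by arm as allocated.
- Multiply impute missing SCID diagnoses whatever the proportion missing, using a small model: arm, baseline OCI-R (OCD subscale) and post-test OCI-R (OCD subscale). Where the post-test score is itself missing, impute it in the same procedure. Adding PHQ-9 and GAD-7 at both times would make seven predictors, too many if there are only about 13 cases.
- Report the risk difference between arms with its confidence interval, adjusted for baseline OCI-R.
- Add a tipping-point table by arm, showing how many cases among those lost would change the conclusion. Imputation corrects only for loss explained by the scores in the model, and this table covers the rest.
- Keep the complete-case chi-square as a sensitivity analysis.
- State whether the 10% rule applies to the questionnaire scores only, and reconcile the two follow-up times.

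The cost is a change of wording and a little more analysis work. No new data are needed. The interval will be slightly wider. According to the Trial status section, analysis begins only once the primary endpoint data are complete, so at submission there was still time to make the change before analysis.
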